| Primary  Endpoints | HIV disease progression, defined as time to:  1) CD4+ cell count decline to 250/μL or below;  2) development of an AIDS-defining condition (WHO Staging criteria); or,  3) death. |
| Secondary  Endpoints | Response to antituberculosis therapy:  sputum AFB clearance by one and two months  rates of TB treatment failure  rates of TB relapse  microbiologic cure of TB  Safety:  Development of antiretroviral drug resistance  Toxicity and side effects  Paradoxical reactions |
| Statistical &  Analytic Plan | The sample size for the trial is 350 HIV-infected TB patients - 175 randomized to punctuated therapy and 175 randomized to anti-TB treatment only and delayed ARV therapy. The sample size provides a power of 80 – 90% to detect an effect size of 35% or greater for HIV disease progression. This effect size translates into an average delay of about one year before the need to start ARV therapy.  The intent-to-treat approach will be used to compare the rate of HIV disease progression between TB patients randomized to receive either punctuated or delayed ARV therapy.  Analysis – Specific Aim 1  The primary outcome for the study is HIV disease progression. The primary analysis of the study will compare  The failure-time distribution of the treated to the reference group.  The change in CD4+ count over time in each group.  Life-table, failure-time, and repeated measures methods will be used to analyze the data.  Analysis – Specific Aim 2  The effect of ARV treatment on the response to antituberculosis therapy will be evaluated by comparing  The proportion of subjects with negative smears or cultures at one and two months (chi square test).  Treatment failure rates between groups  Relapse tuberculosis rates  Life-table, failure-time, and person-year methods will be used in this analysis.  Analysis – Specific Aim 3  The safety of the study intervention will be examined by summarizing the incidence rate and cumulative proportion of severity grade III/IV adverse events according to each study arm.  Life table and descriptive methods will be used.  Additional analyses  In addition to these analyses, the study will examine viral dynamics, emergence of antiretroviral drug resistance, and reconstitution of the host immune response. |

#

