**Table 3. Daily dosages for standard first line anti-TB drugs**

| **Drug** | **Body weight**  **< 50 kg** | **Body weight**  ** 50 kg** |
| --- | --- | --- |
| Isoniazid | 300 mg/d | 300 mg/d |
| Rifampicin | 450 mg/d | 600 mg/d |
| Ethambutola | 800 mg/d | 1200 mg/d |
| Pyrazinamide | 1.5 gm/d | 2 gm/d |

a  15 mg/kg/d

If a patient who initially weighs < 50 kg gains weight during treatment such that he or she weighs  50 kg, the patient’s doses will be increased according to the dosing chart. Pyridoxine 50 mg PO will be administered daily to all subjects during TB treatment to prevent INH-related neurotoxicity.

## 5.2 Study Intervention – Step 2

When eligibility for Step 2 is confirmed, patients will be randomized to receive either immediate six-month punctuated ARV treatment consisting of abacavir, zidovudine, and lamivudine (as Trizivir®) or continuation of anti-TB treatment only with delayed, open-label ARV treatment regimen. Randomization will occur at the time the patient is assessed and meets criteria to start the Trizivir-based punctuated ARV intervention.

Patients will be evaluated at entry into Step 2 with the following pre-ARV (baseline): assessment

1. HIV RNA Roche Amplicor;
2. Plasma storage;
3. PBMC storage/ immune function (Flow cytometry to assess cell surface activation markers, EliSpot to assess CD4 and CD8 T cell specificity to HIV and microbial peptides, Whole blood assays to determine antigen specific response to HIV and microbial antigens)

and, initiated either on the study intervention of six-month punctuated course of Trizivir® or continue with anti-TB treatment only, according to randomized assignment.

Antiretroviral therapy will be started regardless of random assignment in the intervention period when either 1) two CD4+ counts (within 3 months) drop to < 250/µL or 2) an AIDS-defining condition develops as defined by WHO stage IV AIDS-defining condition or a definitive diagnosis of a severe bacterial infection that meets WHO Stage 3 classification (Appendix II). Subjects who do not reach a study outcome during the study period will not enter Step 3 and therefore not be offered daily ARV therapy.

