### **7.4.2 Post- Primary Outcome - Antiretroviral Therapy Follow-up Visits**

Prior to being started on self-administered ARV therapy and entry to STEP 3, a pre-ARV baseline evaluation will be completed; this will include the following examination (appendix I, Step 3):

1. HIV RNA Roche Amplicor
2. Quality of life assessment
3. Plasma storage
4. PBMC storage/ immune function (Flow cytometry to assess cell surface activation markers, EliSpot to assess CD4 and CD8 T cell specificity to HIV and microbial peptides, Whole blood assays to determine antigen specific response to HIV and microbial antigens)

Assessments from confirmation of study outcome, or ARV safety evaluation may be used for pre-antiretroviral baseline if they were completed within two weeks before ARV baseline.

Patients will then be started on self-administered, ARV therapy and enter STEP 3 (Section 5.0 describing the initiation of therapy). Patients will receive detailed counseling about treatment with antiretroviral therapy. They will be informed that adherence measures will be made including unannounced home visits to record self-reported adherence and pill counts. Below is the schedule for STEP 3:

1. Medical history and physical examination including weight (Week 2, months 1, 2, 3, 6, 9, 12, 15, 18, 21, 24, 27, 30, 33, 36, and then every 4 months or as clinically indicated)
2. Adverse experiences survey (Week 2, months 1, 2, 3, 6, 9, 12, 15, 18, 21, 24, 27, 30, 33, 36, and then every 4 months or as clinically indicated)
3. New diagnoses and/or hospitalizations since the last study visit (Week 2, months 1, 2, 3, 6, 9, 12, 15, 18, 21, 24, 27, 30, 33, 36, and then every 4 months or as clinically indicated)
4. Urine or serum -HCG pregnancy test (if suspect)
5. CD4+ lymphocyte count (months 3, 6, 12, 18, 24, 30, 36, then every 4 months thereafter or as clinically indicated)
6. CBC with differential and platelet count (months 3, 6, 12, 18, 24, 30, 36, then every 4 months thereafter or as clinically indicated)
7. Posterior-anterior chest X-ray (as clinically indicated)
8. Sputum semi-quantitative AFB smear and culture on solid media X 2 (as clinically indicated)
9. MTB drug susceptibility (as clinically indicated)
10. Serum aspartate aminotransferase (AST), serum bilirubin (months 1, 2, 6, 12, 18, 24, 30, 36, and every 4 months thereafter or as clinically indicated)
11. Serum creatinine (as clinically indicated)

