The primary outcome for the study is HIV disease progression. This is defined as the time interval between enrollment and the development of one or more of the following endpoints, whichever occurs first: decline of CD4+ count < 250/µL, new AIDS-defining condition, or death. When a subject has met the criteria for primary outcome for CD4+ counts, the date for the first of 2 consecutive CD4+ counts will be used to mark failure time. The primary analysis of the study for each outcome will be to compare the failure-time distribution of the treated to the reference group. Separate failure-time distributions will be estimated for each treatment group using the Kaplan-Meier method78 and compared using the log-rank test.79 Stratified analysis will be performed for the primary outcome according to categories of baseline viral load.80 A Cox proportional hazards regression model81,82 will be developed to evaluate the effect of treatment on disease progression. In these analyses, the failure event will be HIV disease progression; subjects will be censored because of withdrawal during the study or at end of study. We will assess whether censoring is independent of study outcome as this is a fundamental assumption of survival analysis. In these regression models, observed event-free survival will be the dependent variable.

The basic Cox proportional hazards model for this analysis will be formulated as follows:

where h (t,X) is the observed hazard, h0 (t) is the baseline, unmeasured hazard for disease progression, β is the regression coefficient for treatment, ARV is the variable coding for immediate versus delayed ARV treatment (1 and 0, respectively), i the vector of regression coefficients for the covariates, Xi is the vector of covariates that may include time since treatment. This vector will contain known prognostic factors for HIV infection in Africa such as age, tuberculin skin test, baseline CD4+ count, hemoglobin, and performance status. This vector of covariates will also include the time period between initiating antituberculosis therapy and date of randomization to account for varying times in initiating antiretroviral therapy. The assumption of proportional hazards will be tested using graphical methods and formal statistical tests. If this assumption does not hold, then stratified Cox regression models will be developed, stratifying on the variable with non-proportional hazards.

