In addition to the main outcome, we will determine whether the study interventions alter the rate of decline in CD4+ counts by using a linear spline model with 2 time periods. The follow-up period will be divided into two periods: period 1 - from baseline until 6 months; period 2 - from 6 months until CD4+ count falls below 250/µL. Separate slope parameters will be fit for period 1 and period 2 using the linear spline model with a knot, t*, at 6 months. This approach will allow us 1) to analyze the magnitude of effect achieved during the punctuated treatment during period 1 and 2) to compare the rates of decline for the different treatment groups in period 2. The general model is given by:

where yij is the CD4+ count for subject i (i = 1,2, … n) and measurement j (j = 1, 2, … m), G represents the two mutually exclusive treatment groups (punctuated ARV vs. reference group), and t* = 6 months on study. Using appropriate contrasts, we can test for differences in **11G between the groups assigned to punctuated therapy or delayed therapy for period 1. In this analysis, the main interest is not whether there will be a difference in CD4+ slope between the treated and delayed group, but instead what is the magnitude of the difference. This information will be useful in analyzing the response during period 2. Again using appropriate contrasts, we will compare the slopes of the two treatment groups during period 2. The null hypothesis for this analysis is: **2Punct ARV = **2Delay ARV;; the alternative hypothesis is that the two groups will have different slopes in CD4+ measurement. To perform this analysis, we will use the linear mixed-effects model.85

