The main objective of this analysis is to determine whether punctuated ARV given during TB jeopardizes the response to continuous ARV therapy when given to participants who develop CD4+ count < 250/µL. In this analysis, there are 3 major outcomes of interest: CD4+ response, viral dynamics, and viral resistance to ARVs. Safety in terms of toxicity will also be evaluated. In terms of the CD4+ response, we will extend the linear spline model to include another knot, t**, at the time when an individual reaches CD4+ count < 250/µL. This modification of the model will allow us to compare the slope among patients who received punctuated therapy and those who did not. Viral dynamics, viral resistance and safety will be analyzed.

Ancillary Analyses

*Immunologic and Viral Dynamics (see appendix X.)*

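### Period 2 of the CD4 slope model ends only at CD4 below 250, so patients who start ARV for a clinical event at a higher count stay in it with on-treatment counts

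*Protocol*

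**What the plan says.** The rate of CD4 decline is part of the primary objective (Protocol 2.1). The synopsis lists "The change in CD4+ count over time in each group" within the primary analysis for Aim 1. Section 10.2.2.1 fits a linear spline with a knot at 6 months and compares the arms' slopes after it. The second segment is defined as "period 2 - from 6 months until CD4+ count falls below 250".

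Section 5.2 gives two routes to treatment. "Antiretroviral therapy will be started regardless of random assignment in the intervention period" on a confirmed CD4 count below 250, or when "an AIDS-defining condition develops as defined by WHO stage IV AIDS-defining condition or a definitive diagnosis of a severe bacterial infection" is present. The second route has no CD4 condition. Such clinical events are also primary outcomes in their own right: "whichever occurs first: decline of CD4+ count < 250/µL, new AIDS-defining condition, or death" (10.2.2.1).

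Once ARV has started, Step 3 continues to schedule "CD4+ lymphocyte count (months 3, 6, 12, 18, 24, 30, 36, then every 4 months thereafter or as clinically indicated" (7.4.2). For the phase on continuous ARV, section 10.2.2.3 extends the model with "another knot, t, at the time when an individual reaches CD4+ count" below 250, so the later knot follows the same CD4 rule and not the start of treatment.

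**The concern.** The period-2 contrast is meant to show whether CD4 falls more slowly after a six-month course than without one. The response to continuous ARV is a separate question, taken up in 10.2.2.3. The stated boundary separates the two only for patients who reach ARV through a low count. A patient who starts ARV for a clinical event at, say, 400 cells has not met the end-of-period rule. If the count then holds or rises on treatment, that patient may stay in period 2 until the study closes, which can be up to five years after enrolment (7.3.3). The extra knot does not help, because it too waits for a count below 250.

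At stake is the estimate of a quantity named in the primary objective. Each arm's decline would look slower than it is, and the difference between arms would carry a bias that depends on how often each arm starts ARV for clinical reasons.

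**Working it through.** **1. The two routes side by side**

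| Route to ARV | Period 2 as written | Later knot as written |
|---|---|---|
| Confirmed CD4 below 250 | closes | placed |
| Stage IV condition or severe bacterial infection, CD4 above 250 | stays open | not placed |

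No section of the protocol ends the period, adds a knot or drops counts at ARV start on the clinical route.

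**2. Expected direction**

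Let g be the monthly CD4 change on ARV. For each month of on-ARV counts kept in period 2, a patient's trajectory departs from the untreated one by g + 8.5 cells in the reference arm (8.5 is the midpoint of the 7 to 10 cells/month in 10.1) and by g + 5.5 in the punctuated arm (5.5 is assumed). At g = 5 these are 13.5 and 10.5. The steeper arm is therefore displaced more per patient, so the difference shrinks even at equal event rates. It shrinks further if the delayed arm has more clinical events, as the trial hypothesis implies.

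**3. Size by simulation**

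The protocol gives no effect size or power for the slope, so there is no figure of its own to reproduce.

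- From the protocol: 175 per arm, its CD4 visit times, follow-up of 24 to 60 months, a 6-month knot, and a reference slope of -8.5 cells/month.
- Assumed: punctuated slope -5.5 (true difference 8.5 - 5.5 = 3.0); baseline CD4 mean 520; between-patient SD 110; residual SD 70; slope SD 3; CD4 change on ARV of 0 to +10 cells/month for up to 24 months; clinical ARV starts of 1 to 10 per 100 person-years.
- Model: random intercept and slope, generalised least squares with known variance components.

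With no clinical starts the fitted difference is 2.98. Change = (difference as written / 2.98) - 1.

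| Clinical starts per 100 person-years, delayed / punctuated | Difference as written (ARV change 0 to +10) | Change | Stopped at ARV start (ARV change +5) |
|---|---|---|---|
| 1 / 0.65 | 2.77 to 2.87 | -4 to -7% | 2.98 |
| 2 / 2 | 2.77 to 2.84 | -5 to -7% | 2.99 |
| 2 / 1.3 | 2.58 to 2.77 | -7 to -13% | 2.99 |
| 5 / 5 | 2.44 to 2.63 | -12 to -18% | 3.00 |
| 5 / 3.25 | 2.03 to 2.46 | -17 to -32% | 3.00 |
| 10 / 6.5 (ARV change +5 only) | 1.63 | -45% | 3.01 |
| 3.25 / 5 | 2.93 to 3.06 | -2 to +3% | 3.00 |
| 2 / 4 | 3.05 to 3.28 | +2 to +10% | 3.00 |

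The fitted reference slope moves from -8.52 with no clinical starts to between -8.31 and -8.09 at 1 start per 100 person-years, -8.14 and -7.70 at 2, and -7.63 and -6.63 at 5.

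**4. Consequence for a test of the slope**

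The simulated standard error is about 0.46. Power = Φ(f × δ / 0.46 - 1.96), where δ is the true difference and f the retained fraction. At δ = 3.0 power stays near 100%, so the harm is to the estimate. At a smaller δ of 1.3, power is 81% with f = 1, 76% with f = 0.94 and 72% with f = 0.90. These figures rest on the assumed variances.

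**The case against.** The best counter-argument is that a CD4 count below 250 is shorthand for the primary outcome. The subheading in 10.2.2.1 that mentions only that threshold introduces the full composite. A heading in 10.2.2.3 couples the threshold with the start of continuous ARV. Section 3.1 lists every trigger and then restates only the CD4 one. The follow-up after month 6 is labelled as preceding the study outcome (7.3.3 and the Step 2 schedule in Appendix I), and the Step 3 schedule is headed as serving the secondary objectives. This makes the intended meaning plausible, and it means the protocol nowhere says outright that Step 3 counts enter the Aim 1 slope. But none of these headings changes the boundary that is written, and if shorthand was meant, the fix only records it.

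Intention to treat does not settle the matter. It governs analysis by assigned arm and gives no reason to close the period for one route to ARV and leave it open for the other. Nor is this a detail left to the analysis plan, since the protocol states the boundary and states it incompletely.

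Three stronger readings are tempting and are not supported.

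- That the difference necessarily shrinks. It was about neutral at 3.25/5 starts per 100 person-years and wider at 2/4.
- That clinically treated patients never leave period 2. Counts may still fall below 250 on failing ARV, and patients with contraindications stay untreated in Step 2 (5.3) and contribute genuine untreated counts.
- That a third of the effect is lost. Losses of that order need about 5 or more clinical starts per 100 person-years in the delayed arm, and the protocol gives no such rate. Section 8.1.1 does not expect many opportunistic infections, though it says so only for the intervention period, before period 2 begins.

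**Conclusion.** The point holds in a conditional form. Applied as written, the period-2 rule and the later knot mix on-ARV counts into a slope named in the primary objective, for one of the two routes to treatment. Decline is understated in any arm that has clinical starts. The between-arm difference would be expected to shrink if clinical starts are equally frequent or more frequent in the delayed arm; it could be unchanged or widened if they are clearly more frequent in the punctuated arm, roughly one and a half times or more in these simulations.

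The size cannot be fixed from the protocol. The 4 to 13% range belongs to assumed rates of 1 to 2 starts per 100 person-years in the delayed arm (scenarios 1/0.65, 2/2 and 2/1.3), with the slopes, variances and on-ARV changes assumed above; the loss grows at higher rates. A reader might infer that the trial's main result is compromised. It is not: the log-rank and Cox analysis counts clinical events as outcomes and does not use counts taken after them, and 10.2.2.1 presents the slope as additional to that outcome. The correction should be made, but the design does not depend on it.

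**What to change.** In 10.2.2.1, define period 2 as running from 6 months until the first of the CD4 outcome (below 250) or the start of post-outcome (Step 3) or non-protocol ARV. State that CD4 counts taken after that start are excluded from the Aim 1 slopes in both periods; the assigned punctuated course does not count as such a start. In 10.2.2.3, place the later knot at the start of continuous ARV.

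This is a small change of wording. It needs the ARV start date, which Step 3 follow-up already depends on, and alters no treatment, visit or sample size. The cost is fewer late CD4 counts. Stopping at ARV start also relies on the missing-at-random assumption behind the likelihood-based analysis that 10.2.2.1 already plans.

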#### **10.2.2.2 Specific Aim 2**

To determine whether a punctuated six-month course of ARV therapy during treatment of active TB will improve the response to antituberculous therapy, as measured by one month culture conversion, treatment failure, and relapse TB, among patients with active TB and CD4+ cell count above 350 cells/µL.

The analysis of this Specific Aim will include only patients with active TB that have been randomized in the clinical trial. The effect of ARV treatment on the response to antituberculous therapy will be evaluated by comparing the proportion of subjects with negative smears or cultures at one and two months (chi square test). A similar analysis will be performed for antituberculosis treatment failure in the ARV treatment arms compared to the reference arm.

Previous published studies of TB in HIV infection estimate relapse rates between 3 and 10%; we thus expect to identify between 10 to 35 relapse cases of TB during the study. The cumulative incidence of TB relapse will be estimated by group using Kaplan-Meier methods; incidence density methods will also be used to measure the number of relapses per 100 person-years of observation after completing antituberculous treatment according to ARV treatment group. The incidence density ratio (95% confidence interval) will be estimated to compare incidence in treated and reference groups. Cox regression analysis will be used to determine whether punctuated ARV therapy is associated with relapse after adjusting for covariates. The analysis will account for the different treatment histories by using time-dependent Cox proportional hazards analysis. The analysis will be further stratified according to relapses due to reactivation and reinfection based on the RFLP patterns.

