## 2.2 Secondary Objectives

1. To determine whether a punctuated six-month course of ARV therapy during treatment of active TB will improve the response to antituberculous therapy, as measured by one and two month culture conversion, treatment failure, and relapse TB, among patients with active TB and CD4+ cell count above 350 cells/µL.
2. To determine whether a punctuated six-month course of highly active ARV therapy is safe when given with antituberculosis therapy as measured by development of ARV drug resistance, toxicity and side effects, and paradoxical reactions.

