## Inclusion

## Inclusion Criteria for Study Entry

Screening evaluations to determine eligibility must be completed within 14 days prior to study entry unless otherwise specified.

1. AFB Smear-positive or culture-positive, presumed pulmonary TB
2. Patients, male or female, aged 13-60 years
3. HIV seropositive (at any time)
4. CD4+ count > 350 cells/ml
5. Residence within 20 km of Kampala

6 Female study volunteers of reproductive potential (defined as girls who have reached menarche or women who have not been post-menopausal for at least 24 consecutive months, i.e. who have had menses within the preceding 24 months, or have not under-gone surgical sterilization (e.g. hysterectomy, bilateral oophorectomy, or salpingotomy) must have a negative serum or urine pregnancy test performed within 14 days prior to study entry.

1. If participating in activity that could lead to pregnancy, the female study volunteer must use a reliable method of contraception while receiving protocol-specified medication(s) and for 6 weeks after stopping the medications(s).
2. If the female volunteer is not of reproductive potential (girls who have not reached menarche, women who have been post-menopausal for at least 24 consecutive months, or women who have undergone surgical sterilization, salpingotomy) she is eligible without requiring the use of contraception.

7 Ability and willingness of subject or legal guardian to provide informed consent for study participation

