## 6.2 Response to Antituberculosis Therapy

### **6.2.1 Sputum Culture Conversion**

The proportion of patients with MTB sputum conversion (from positive to negative) per treatment group will be determined at months 1 and 2. For an individual patient, sputum culture conversion will be defined as the absence of mycobacterial growth on solid media without a subsequent positive sputum culture during the first 16 weeks of therapy. Subjects with all sputum cultures negative at 2 consecutive time points who are clinically stable or improving and unable to produce sputum will be considered to have converted their sputum at the date of the first of the two specimens. Patients with one negative sputum culture after a period of treatment, who are clinically stable or improving and unable to produce sputum thereafter, will be considered to have converted their sputum culture at the time of the first specimen.

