### **6.2.4 Clinical Cure of TB**

Clinical cure of TB is defined as a patient who (1) has completed anti-TB therapy (6.2.2); (2) has a negative smear or culture when last tested; (3) no new lesions on chest x-ray; and (4) no clinical signs or symptoms of active TB.

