### **6.2.5 Treatment Failure**

A culture-positive treatment failure is defined as a patient who is receiving anti-TB treatment and has at least one sputum mycobacterial culture growing at least 5 colonies of *M. tuberculosis* (MTB) on solid medium after completing 4 or more months of effective anti-TB treatment. Patients who default before completing anti-TB treatment and return later with culture-positive tuberculosis will be termed failures after non-adherence.

Patients will be retreated in accordance with applicable national TB program guidelines and drug susceptibility testing results.

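### Aim 2 tests negative smears or cultures at one and two months, not the culture conversion set as the objective, and clinical cure and treatment failure can overlap

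*Protocol*

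**What the plan says.** **Objective.** Section 2.2 judges TB response "as measured by one and two month culture conversion, treatment failure, and relapse TB".

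**Definition.** Section 6.2.1 asks for a change from positive to negative at months 1 and 2. It states that "sputum culture conversion will be defined as the absence of mycobacterial growth on solid media without a subsequent positive sputum culture"; this last condition covers 16 weeks from the start of treatment.

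**Analysis.** The aim sentence of Section 10.2.2.2 is worded "as measured by one month culture conversion, treatment failure, and relapse TB", so it names one month only. The analysis paragraph below it evaluates the effect by "comparing the proportion of subjects with negative smears or cultures at one and two months (chi square test"), restricted to randomized patients with active TB. It does not refer to 6.2.1. The Synopsis analysis plan repeats it: "The proportion of subjects with negative smears or cultures at one and two months (chi square test"). The Synopsis list of secondary endpoints and Section 3.1 speak instead of sputum clearance by one and two months.

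**Entry.** The first inclusion criterion is "AFB Smear-positive or culture-positive, presumed pulmonary TB". Section 4.5 also accepts either test, while Section 4.1 describes the population as smear-positive.

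**Cure and failure.** Under Section 6.2.4 a clinical cure needs, among other things, a patient who "has a negative smear or culture when last tested". Under Section 6.2.5 a treatment failure is a patient on treatment who "has at least one sputum mycobacterial culture growing at least 5 colonies of" *M. tuberculosis* after four or more months of effective treatment. Microbiologic cure (6.2.3) rests on cultures alone. Table 6 lists cure and treatment failure under Aim 2 without saying which cure.

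**The concern.** The quantity to be tested differs from the stated objective in three ways: smear is admitted alongside culture, a negative state replaces a change from positive, and the condition of no later positive culture is gone. The trial is open-label and the protocol does not say which result answers the objective, so the choice could be made after the data are seen. The contrast can also be diluted by patients who have no change to show.

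A second, separate matter is that the wording of clinical cure lets a patient who meets the failure definition be a cure as well. If both categories were tabulated, they would not add up.

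**Working it through.** **1. The protocol's own figure.** The only design figure covering this comparison is the statement in Section 10.1 that secondary outcomes have at least 80% power. No conversion rates are given, so it can be neither reproduced nor refuted. Inputs that are given: 175 per arm and two-sided alpha 0.05 (the latter stated for the primary outcome). For two proportions,

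power = Φ{ [ |p₂ − p₁| − 1.96·√(2p̄(1 − p̄)/n) ] / √[(p₁(1 − p₁) + p₂(1 − p₂))/n] }, where p̄ is the mean of p₁ and p₂.

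With n = 175 this reaches 80% for about 40% vs 55%, 60% vs 74%, or 80% vs 91%. These rates are assumptions.

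**2. The endpoints side by side.**

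| | 2.2 and 6.2.1 | 10.2.2.2 and Synopsis analysis |
|---|---|---|
| Test | culture, solid media | smears or cultures |
| Baseline | must be positive | not mentioned |
| Later positive culture, first 16 weeks | cancels conversion | not mentioned |
| Times | months 1 and 2 | months 1 and 2 (aim sentence: month 1) |

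**3. Already negative at entry.** The inclusion criterion admits a smear-negative, culture-positive patient, who is smear-negative from day 0. It also admits a smear-positive patient whose screening cultures are negative, who cannot convert on culture. If a share s of each arm is negative on a test at entry and stays so, the observed difference on that test is (1 − s) times the difference among those positive at entry. The protocol gives no s.

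**4. Reversion.** A patient culture-negative at month 1 and positive at month 2 is not converted at month 1 under 6.2.1 but is negative at month 1 under 10.2.2.2. Section 7.3.2 schedules sputum at weeks 4–6, 8 and 18–20. On scheduled samples, then, the 16-week condition can change only the month 1 result, through the week 8 culture. The next sample falls outside 16 weeks.

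**5. If either negative test suffices.** Let p be the culture-negative share and f the share of culture-positive patients with a negative smear, equal in both arms. The share counted negative is p + (1 − p)f, so the difference shrinks by the factor (1 − f). For 40% vs 55% and f = 20%: 0.40 + 0.60 × 0.20 = 0.52 and 0.55 + 0.45 × 0.20 = 0.64. Every p and f below is assumed.

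| Culture-negative | f = 0 | f = 20% | f = 40% | f = 60% |
|---|---|---|---|---|
| 40% vs 55% | power 80.5% | 52 vs 64: 62.4% | 64 vs 73: 44.1% | 76 vs 82: 28.0% |
| 60% vs 75% | power 85.3% | 68 vs 80: 72.7% | 76 vs 85: 56.6% | 84 vs 90: 38.5% |
| 70% vs 83% | power 82.1% | 76 vs 86.4: 70.4% | 82 vs 89.8: 55.5% | 88 vs 93.2: 38.4% |

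**6. Cure and failure together.** Four months is 4 × 52/12 = 17.3 weeks, so the sample at weeks 18–20 can establish failure. Take a patient whose culture then grows at least 5 colonies, whose smear is negative, who takes all the drugs, and who has no symptoms and no new X-ray lesions. That patient meets 6.2.5 and also 6.2.4, because a negative last smear is enough. The definition of completion in 6.2.2, which 6.2.4 cites, has no bacteriological condition. Section 5.1.1.1 adds a response to treatment but accepts a clinical one. No text ranks the two categories.

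**The case against.** The strongest reply is that the phrase can mean two separate comparisons, one of smears and one of cultures. Nothing in 10.2.2.2 or the Synopsis sets a per-patient rule under which either negative result suffices. A reader might infer that culture-positive patients are simply scored as responders. The documents do not support that: it needs the either-test reading, and even then only smear-negative culture-positive patients are affected. Smear clearance is also arguably a listed endpoint, and 6.2.1 gives a sound culture-only definition. This part stands, and it removes the power table as a finding. It does not remove the mismatch: under two comparisons, patients negative at entry and patients who revert still count as negative, and which comparison answers the objective is still unstated.

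On entry, Section 4.1 says smear-positive, and Section 4.4 provides for final eligibility after review of all sputum cultures. But the inclusion criterion and 4.5 say otherwise, and the only exclusion that 4.4 attaches to that review is multi-drug resistance.

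On cure, a reader might infer inflated cure proportions or contradictory secondary results. No analysis names clinical cure, the Synopsis endpoint is microbiologic cure, the overlapping patient is narrowly defined, failures are to be retreated, and a blinded committee classifies outcomes. The inflation is therefore not shown. The overlap in the definitions is, since the committee is given no rule for such a patient.

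**Conclusion.** The contradiction holds on the text alone: 10.2.2.2 and the Synopsis test a negative state on smears or cultures, whereas 2.2 and 6.2.1 call for culture conversion. The aim sentence adds a third variant by naming one month only. Patients negative at entry and those who revert count as responders on any reading. Smear-negative patients still growing *M. tuberculosis* count only if either test suffices.

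The effect on the Aim 2 contrast cannot be sized from the documents. The power figures show direction under assumed rates, an equal f in both arms and the either-test reading; they are not estimates for this trial. Randomization still makes a test of no difference fair. What suffers is its meaning and probably its sensitivity.

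The overlap of 6.2.4 with 6.2.5 is a real gap in the definitions with no demonstrated effect on a planned comparison. Both matters concern secondary outcomes. They should be corrected, but the primary analysis is untouched.

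**What to change.** - In 10.2.2.2 and the Synopsis, make the month 1 and month 2 comparison the culture conversion of 6.2.1, among randomized patients with a positive screening culture, and bring the aim sentence into line. Screening sputum is taken before randomization, so this restriction keeps the randomized comparison intact.
- Report smear conversion as a separate result, among those smear-positive at screening.
- Reconcile 6.2.4 with 6.2.5 so that a patient classified as a treatment failure is not also counted as a clinical cure in the analysis. State in Table 6 which cure is analysed.
- Reconcile Section 4.1 with the inclusion criterion on smear status.

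The cost is wording. Three screening sputum samples and the on-treatment cultures are already scheduled. The conversion denominator becomes slightly smaller, because patients with a negative screening culture leave that comparison; they can stay in the other Aim 2 analyses.
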